***Primary outcome***		
Health-related quality of life	Mean change in EQ-5D-5L value (utility) from baseline to 12 months (primary outcome)	Baseline, 6 months, 12 months
***Secondary outcome***		
Dialysis withdrawal	Number of participants identified as withdrawal from dialysis	12 months—collected through ANZDATA
Health-related quality of life	Mean change in EQ-5D-5L value (utility) from baseline to 6 months	Baseline, 6 months
Health-related quality of life	Mean change in EQ-5D-5L and VAS scores from baseline at 6 months; and from baseline to 12 months	Baseline, 6 months, 12 months
Overall survival	All-cause mortality rates at 12 months	12 months
Cause-specific mortality (including deaths due to dialysis withdrawal)	Cause-specific mortality rates at 12 months for dialysis withdrawal, cardiovascular, cancer, infection and other causes	12 months
Fatigue	Mean change in SONG-HD Fatigue score at 12 months	Baseline, 6 months, 12 months
Symptom severity	Intervention arm only. Measured by change in IPOS-Renal symptom severity scores	Baseline, 3 months, 6 months, 9 months, 12 months
Haemodialysis duration	Average number of hours per treatment	12 months—collected through ANZDATA
Haemodialysis frequency	Number of treatments per week	12 months—collected through ANZDATA
Haemodialysis adequacy	Urea reduction ratio and Kt/V	12 months—collected through ANZDATA
Symptom-related and general healthcare utilisation	Hospitalisations, Medicare Benefits Schedule (MBS), Pharmaceutical Benefits Scheme (PBS) items	Assessed through linked administrative records for admitted patient data and Medicare claims
Cost-effectiveness	Incremental cost per quality-adjusted life year (QALY) gained reported as an incremental cost effectiveness ratio (ICER) or incremental net benefit (INB)	12 months; EQ-5D-5L utilities collected as per primary outcome; healthcare use identified from linked administrative records

*Abbreviations: ANZDATA*, Australia New Zealand Dialysis and Transplant Registry; *EQ-5D-5L*, EuroQoL 5-item 5-level preference-based measure of health status; *VAS*, visual analogue scale; *SONG-HD Fatigue*, Standardised Outcomes in Nephrology – Haemodialysis, Fatigue; *IPOS Renal*, Integrated Palliative Outcome Scale – Renal; *Kt/V*, K=dialyser clearance of urea, t=dialysis time, V=volume of distribution of urea, this is approximately equal to the patient’s total body water

Participants in both the control and intervention arms are asked to complete the EQ-5D-5L and Standardised Outcomes in Nephrology-Haemodialysis (SONG-HD) Fatigue measure at baseline, 6 months and 12 months, as well as two fidelity questions regarding whether they discussed any symptoms with their treating health professionals (e.g., dialysis nurse, nephrologist, dietitian, social worker) at their last visit.

EQ-5D-5L, SONG-HD Fatigue measure and the IPOS-Renal responses will be collected from participants during their haemodialysis sessions. They will be completed electronically on an Android tablet provided to the centres by the trial. The data will be stored in Qualtrics (Qualtrics, Utah, 2021) survey platform, securely transferred daily to the SWIFT module within the ANZDATA Registry. Health-related QOL for both groups will be measured using the EQ-5D-5L (5 domains assessing mobility, self-care, usual activities, pain/discomfort, anxiety/depression), each with 5 levels of severity, and the visual analogue scale (VAS) on a 0 to 100 scale (0=worst imaginable health, 100= best imaginable health). QOL will be self-reported at baseline, 6 and 12 months. The EQ-5D-5L takes approximately 3 min to complete and is the most widely used and validated preference-based health-related QOL measure among dialysis patients [17]. It is sensitive to poor health states and high symptom burden associated with haemodialysis treatment [26]. The EQ-5D-5L is the measure that achieves the highest amount of complete data, making it the preferred choice for repeated measures collected within a registry [9]. SONG-HD Fatigue is a core outcome measure in haemodialysis trials and will be assessed using a 3-item questionnaire established by the Standardised Outcomes in Nephrology (SONG) Initiative that has been validated in the haemodialysis population [27]. Permission has been obtained for the IPOS Renal (Kings’ College, London, UK), EQ-5D-5L (EuroQol, Rotterdam, Netherlands) and SONG-HD Fatigue (SONG Initiative, Sydney Australia) to use these instruments in SWIFT via electronic data capture.

### Participant timeline {13}

Participant timeline including recruitment, intervention and outcome measures are displayed in Table 1.

### Sample size {14}

SWIFT will recruit 143 haemodialysis centres (or clusters) in Australia. Recruitment data from the SWIFT pilot study confirmed the assumptions of over 50% patient participation in each centre, and 80% completion of EQ-5D-5L at 12 months [17]. Sites are grouped into clusters (see 16a) of approximately 2 sites/cluster. Approximately seventy-one clusters in each arm (equating to 2422 total participants) will enable us to identify a clinically significant mean (0.07) 7% increase in health-related quality of life (from 0.59 [59%] to 0.66 [66%]) with 90% power. This minimum clinically important difference was determined through review of EQ-5D-5L studies that showed a change in overall utility of between 0.03 and 0.07 across a range of chronic conditions was associated with meaningful and observable improvements in QOL. This minimum effect of 0.07 was considered feasible and is supported by an observational study in New South Wales (NSW) that demonstrated improvement in EQ-5D-5L utility of 0.11 could be achieved with a focus on symptom management (internal publication). The power calculation is based on a two-sided *t*-test with alpha=0.05 and assumes a modest intra-cluster correlation coefficient of 0.1 and a design effect of 3.5 (to account for clustering, allowing for uneven cluster sizes) creating an effective sample size of 692. We assume a standard deviation (SD) of the change between baseline and 12 months of 0.281. The 7% represents a conservative estimate in effect however one which demonstrates a clinically meaningful improvement in QOL and translates to a societal benefit of 640 quality-adjusted life years (QALYs) per year.

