**Methods:**

We are conducting an Australia and New Zealand Dialysis and Transplant (ANZDATA) registry-based cluster randomised controlled trial to determine the clinical- and cost-effectiveness at 12 months, of 3-monthly symptom monitoring using the Integrated Palliative Outcome Scale-Renal (IPOS-Renal) survey with clinician feedback, compared with usual care among adults treated with haemodialysis. Participants complete symptom scoring using a tablet, which are provided to participants and to clinicians. The trial aims to recruit 143 satellite haemodialysis centres, (up to 2400 participants). The primary outcome is change in health-related QOL, as measured by EuroQol 5-Dimension, 5-Level (EQ-5D-5L) instrument. Secondary outcomes include overall survival, symptom severity (including haemodialysis-associated fatigue), healthcare utilisation and cost-effectiveness.

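### The 90% power is computed on all 2,422 participants with no allowance for the plan's own 80% completion at 12 months; allowing for it gives about 89%

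*Protocol article*

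**What the plan says.** All the inputs stand in the protocol article, section Sample size {14}:

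- Completion: pilot data are said to support "80% completion of EQ-5D-5L at 12 months".
- Size: about 71 clusters per arm, "equating to 2422 total participants".
- Target: a "clinically significant mean (0.07) 7% increase in health-related quality of life (from 0.59 [59%] to 0.66 [66%]) with 90% power".
- Test: "The power calculation is based on a two-sided" t-test with "alpha=0.05 and assumes a modest intra-cluster correlation coefficient of 0.1".
- Variability: a "standard deviation (SD) of the change between baseline and 12 months of 0.281".
- Clustering: "a design effect of 3.5 (to account for clustering, allowing for uneven cluster sizes) creating an effective sample size of 692".

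The Methods paragraph of the abstract gives the recruitment aim as "143 satellite haemodialysis centres, (up to 2400 participants".

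Three other places bear on the point. Table 2 defines the primary outcome as the change in utility from baseline to 12 months, so a participant needs a 12-month value to contribute. Section {20c} mentions multiple imputation only as a sensitivity analysis that will be considered for people known to be alive. Section {20a} names a GEE model adjusted for the stratification factors.

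**The concern.** The paragraph states a completion rate and a power, and the second takes no account of the first. If one participant in five has no 12-month EQ-5D-5L, the effective size of 692 describes a trial with complete follow-up, not the trial the paragraph expects.

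Reading 2,422 as the number of completers does not settle the matter. At 80% completion that number needs about 3,028 recruits, and the abstract gives a maximum of 2,400. So either non-completion was left out of the power, or the recruitment figure in the abstract is too low.

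The 90% is the published justification for the size of the trial, and readers will use it to judge how informative a null primary result is. It should follow from the assumptions printed beside it.

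**Working it through.** **Inputs (Sample size {14}).** Difference 0.07; SD of change 0.281; two-sided alpha 0.05; ICC 0.1; design effect (DE) 3.5; 2,422 participants; about 142 clusters (71 per arm); 80% completion. The abstract adds recruitment of up to 2,400.

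**1. The plan's own figure.**
- Required n per arm = 2 × (1.960 + 1.282)² × 0.281² / 0.07² = 339 by the normal approximation, and 340 with the noncentral t. That is 680 effective in total.
- 680 × 3.5 = 2,380 participants analysed.
- 2,422 / 3.5 = 692.0 exactly. With 346 per arm, 0.07 / (0.281 × √(2/346)) = 3.28, and power is 90.5% (noncentral t).

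The stated 692 and 90% therefore reproduce, but only without any allowance for missing 12-month data. About 2,380 / 2,422 = 98% of participants must be analysed at DE 3.5.

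**2. Expected completers.**
- 0.80 × 2,422 = 1,938.
- 0.80 × 2,400 = 1,920.

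**3. Design effect at the analysed cluster size.** The usual formula for unequal clusters is DE = 1 + [(CV² + 1) × m − 1] × ICC, where m is the mean cluster size and CV is the coefficient of variation of cluster size. The article does not give the CV, so it is back-solved.
- Before loss: m = 2,422 / 142 = 17.06. Setting DE = 3.5 with ICC 0.1 gives (CV² + 1) × m = 26, so CV is about 0.72.
- After loss: m = 0.80 × 17.06 = 13.65. With the CV unchanged, (CV² + 1) × m = 0.80 × 26 = 20.8, so DE = 1 + (20.8 − 1) × 0.1 = 2.98.

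The value 2.98 depends only on the ICC and on the CV staying the same. Using 143 clusters instead of 142 gives the same result.

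**4. Resulting power (noncentral t).**

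| Recruited | Analysed | DE | Effective size | Power |
|---|---|---|---|---|
| 2,422 | 2,422 | 3.5 | 692 | 90.5% |
| 2,422 | 1,938 | 2.98 | 650 | 88.7% |
| 2,400 | 1,920 | 2.98 | 644 | 88.4% |
| 2,422 | 1,938 | 3.5 (kept) | 554 | 83.3% |
| 2,400 | 1,920 | 3.5 (kept) | 549 | 82.9% |

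**5. The alternative reading.** If 2,422 are completers, recruitment must be 2,422 / 0.80 = 3,028, against up to 2,400 in the abstract.

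**The case against.** The best case for the plan has four parts.

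*The loss is small.* The number of clusters is fixed, so losing participants within clusters also lowers the design effect. On that basis power falls by only 1 to 2 points. This stands, and it determines the size of the point. A reader might infer that power really drops to 83%. That figure applies a design effect meant for about 17 participants per cluster to clusters of about 13.6, so it holds only if 3.5 is kept as printed.

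*The count is ambiguous.* The article never says that 2,422 means recruits; it could already be net of non-completion. This is possible, but then the abstract's recruitment figure is wrong. The near match between 2,400 and 2,422 favours recruits.

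*There is some slack.* A reader might infer that every one of the 2,422 must be analysed. About 2,380 would do, and 2,400 analysed would still give 2,400 / 3.5 = 686 effective, about 90.3%. The slack is about 2%, not 20%.

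*The planned analysis may be more efficient than a t-test.* An adjusted GEE could recover the difference: √(650 / 680) = 0.978, so a residual SD about 2% below 0.281 would restore 90%. The article claims no such gain, so it cannot support the stated figure, but it shows how small the gap is.

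A reader might also set the 1,667 dialysis deaths in 2020 against the 13,931 people on dialysis (about 12%), apply this on top of the 80%, and conclude that only about 70% will be analysed. The article does not restrict the 80% to survivors, so this may count deaths twice. The ratio also covers all dialysis patients, including those on peritoneal and home dialysis, and not consenting participants in the trial's centres. That scenario is not supported.

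**Conclusion.** The point holds at a modest size. The stated 90% power makes no allowance for the 80% completion assumed in the same paragraph. If 2,422 counts recruits, the coherent figure is about 89%: 88.7% from 2,422 recruits and 88.4% from 2,400. This rests on an ICC of 0.1, a fixed number of clusters, losses spread so that the cluster-size CV stays near 0.72, and the 80% covering all causes of a missing 12-month value. The CV is back-solved, not documented.

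The shortfall does not show that the trial is seriously underpowered, and it would barely change how a null result is read. It is nevertheless an error in a printed calculation: the completion rate, the participant count, the recruitment figure and the power cannot all be right together.

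**What to change.** State whether 2,422 counts recruits or participants with a 12-month EQ-5D-5L.

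- If recruits: restate the calculation on the expected completers (about 1,920 to 1,938), give the assumed cluster-size CV, recompute the design effect at the analysed cluster size, and report the resulting power in place of 90%. Under the assumptions above it is about 89%.
- If completers: say so, and correct the abstract's recruitment figure to about 3,028.

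The cost is one recalculation and a few sentences. On the first reading the stated power becomes slightly less favourable. Correcting the statement needs no extra enrolment and no change to the design or analysis.

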### Recruitment {15}

Contact details of all potential dialysis centres have been sourced from the ANZDATA registry. Centres are invited via email to complete a pre-trial feasibility survey, exploring existing PROMs use and symptom management strategies. Eligible centres that agree to participate will be randomised. All patients attending that site over a 2-week period are invited to participate in the trial. New patients who may be in their first year of dialysis and who are not yet registered with the ANZDATA registry can be added to the Registry (and trial) before the baseline data collection commences. The ANZDATA Registry operates under an “opt out” model of consent; therefore, if a patient is in a participating centre and chooses not to be a part of the Registry, they are not able to join the trial as secondary outcomes will not be able to be collected for them.

Each patient will be provided with a Participant Information Sheet (PIS) and the opportunity to read the document and ask questions. The PIS was prepared with input from an ANZDATA consumer representative, [name] (SM), and trialled by patients in the Royal Adelaide Hospital haemodialysis unit. Both the PIS and the PIS summary have been translated into the seven language translations used for SWIFT and are presented to patients in the unit. A screening log records any patients who decline participation in SWIFT and representativeness of the included sample will be reported. At the participant’s next dialysis session (at least 2 days later), the participant is asked to complete the online survey(s) specific to their trial allocation (intervention or control). The consent form is embedded into the baseline survey of the trial and will be completed electronically. Participants in both groups will be informed to raise any health concerns with their doctor or nurse.

### Assignment of interventions: allocation

#### Sequence generation {16a}

ANZDATA centres (i.e. clusters) will be randomised to intervention or control. The randomisation takes place, on a state-by-state basis using the method of minimisation as they agree to participate. This occurs once the SWIFT team has received the feasibility forms for all eligible centres in a state and confirmed which sites will participate. Centres (clusters) may consist of more than one site if frequent patient movement or otherwise close institutional linkages between sites prohibit distinction into multiple functionally distinct clusters. The randomisation will be stratified based upon location (state), metropolitan or regional, private or public unit or prior or current use of the IPOS-Renal questionnaire for symptom monitoring within each centre and cluster size. This will diminish potential confounding by these factors.

#### Concealment mechanism {16b}

Once participating sites are confirmed, the allocation process will be undertaken by the trial statistician (CB) and kept concealed until the site initiation visit. Access to the allocations is limited to the CI (RLM), the trial statistician (CB), the CTC trial operations coordinator (PW) and ANZDATA Registry Manager ([name]) to minimise risk of inadvertently influencing sites or prematurely revealing allocation.

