### Who will take informed consent? {26a}

The nurse champion or their delegate (other nursing staff, allied health professionals, clinical research assistants or other nominated persons) in each dialysis centre will assist with recruitment and consent by distributing the patient information sheets prior to survey completion and are available to answer trial-related questions from participants. The nurse champion takes responsibility for conducting the trial in their unit and is responsible for leading participant recruitment. Consent is obtained electronically from each participant prior to commencing the baseline survey.

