### Assignment of interventions: blinding

#### Who will be blinded {17a}

Blinding to allocation is not possible within clusters due to the nature of the intervention; however, all staff compiling and analysing outcome data will be blinded to allocation.

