#### Plans to promote participant retention and complete follow-up {18b}

The SWIFT Pilot Study [17] determined that an important facilitator to the uptake and engagement in the trial was a nurse champion in each centre. These nurse champions influenced the rates of recruitment within each haemodialysis centre. Participant retention is potentially high given that the participants are attending their haemodialysis centre three times per week, unless they receive a transplant, die, stop haemodialysis or are transferred to another non-participating haemodialysis centre. Additionally, consumer involvement in the design of the trial was to aid feasibility. Symptoms are 3 of the top ten patient research priorities [28]. Dialysis patients and their family members have helped select the most meaningful and feasible QOL instruments.

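### Allocation is disclosed at site initiation, on the natural reading before consent and baseline EQ-5D-5L, leaving a risk of differential recruitment that the plan's safeguards narrow but do not remove

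*Protocol article*

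**What the plan says.** All references are to the Protocol article.

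- **Randomisation.** Recruitment {15}: "Eligible centres that agree to participate will be randomised". The invitation of patients is described after this. Sequence generation {16a} adds that randomisation proceeds state by state once the participating sites are confirmed.
- **Concealment.** Concealment mechanism {16b}: the allocation is "kept concealed until the site initiation visit", with access until then limited to four named roles.
- **Who recruits.** Who will take informed consent? {26a}: the unit's nurse champion "is responsible for leading participant recruitment". The champion or a delegate hands out information sheets and answers questions.
- **Blinding.** Who will be blinded {17a}: "Blinding to allocation is not possible within clusters due to the nature of the intervention".
- **Consent and baseline.** Recruitment {15}: "The consent form is embedded into the baseline survey of the trial", and the participant is asked to "complete the online survey(s) specific to their trial allocation (intervention or control". Table 1 places EQ-5D-5L, SONG-HD Fatigue and the questions put to all participants at baseline in both arms, and IPOS-Renal at baseline in the intervention arm only.
- **Primary outcome.** Table 2: mean change in EQ-5D-5L utility from baseline to 12 months.
- **Safeguards.** Recruitment {15}: every patient attending in a 2-week period is invited, decliners are logged and representativeness is reported. Strategies to improve adherence to interventions {11c}: registry staff reconcile the unit's patient list with the registry, and a research assistant from the trial team attends at the start of recruitment where possible.

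**The concern.** Concealment protects the entry of centres but not the entry of participants. In a cluster trial, randomisation balances the centres. It does not balance the people who consent afterwards if those who recruit, or those who are asked, know the arm.

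The article gives reasons why consent could differ between arms. The intervention baseline adds an IPOS-Renal of about 9 minutes to an EQ-5D-5L of about 3 minutes. Intervention participants who supply an email address receive a copy of their results, and severe scores are flagged for clinical review; controls have neither. If, for example, more symptomatic patients joined in intervention units, their baseline utility would be lower, and regression to the mean would make the change score favour the intervention. Higher burden could select in the opposite direction. Baseline EQ-5D-5L is also self-reported by people who may already know their arm.

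**Working it through.** **1. Order of events.** {15} and {16a} put randomisation before patient invitation. {16b} ends concealment at site initiation. {26a} and {17a} put unblinded unit staff in charge of recruitment. {15} places consent inside a baseline survey that depends on the arm. The article does not say outright that site initiation precedes recruitment, but a unit cannot issue arm-specific surveys at consent without the arm being in operation, so this is the natural reading.

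**2. Room for selection.** Sample size {14} assumes participation of over 50% in each centre, so up to about half of those invited may not join.

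**3. The plan's own sample size.** Inputs from {14}: difference 0.07, SD of change 0.281, two-sided alpha 0.05, power 90%, design effect 3.5, effective sample size 692, total 2422.

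- n per arm = 2 × (1.960 + 1.282)² × 0.281² / 0.07² = 339 after rounding up, or 678 in total. This is within 3% of 692.
- 692 × 3.5 = 2422, as stated.
- Power with 346 per arm is 0.906.

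The design figures reproduce, and nothing in this point changes them.

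**4. Illustrative bias.** Assumptions, not document figures: selective consent makes the arms differ by d in baseline mean utility, and the slope of 12-month on baseline utility is b. Without baseline adjustment, the size of the bias in the change score is (1 − b) × d.

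| d | b | Bias | Share of 0.07 |
|---|---|---|---|
| 0.02 | 0.6 | 0.4 × 0.02 = 0.008 | 11% |
| 0.04 | 0.5 | 0.5 × 0.04 = 0.020 | 29% |

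The result is sensitive to the inputs. With d from 0.02 to 0.07 and b from 0.4 to 0.8, the bias runs from 0.2 × 0.02 = 0.004 to 0.6 × 0.07 = 0.042, which is 6% to 60% of the target.

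**5. Against the planned precision.** SE = 0.281 × √(2/346) = 0.0214. A bias of 0.008 to 0.020 is then about 0.4 to 0.9 SE. With no true effect, a bias of 0.01 would raise the two-sided type I error from 5% to about 7.5%, and a bias of 0.02 to about 15%.

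Steps 4 and 5 cover selection on baseline utility only. They do not quantify selection on unmeasured factors or a shift in how baseline is reported.

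**The case against.** The strongest case against is that little room is left for selection. Every attendee in a fixed window is invited, so champions do not choose whom to approach. The list of eligible patients is reconciled with the registry. A research assistant supports the start of recruitment where possible. The information sheet is described as a single document, handed out at least 2 days before the survey, and nothing says that it differs by arm. The extra burden is one questionnaire completed during dialysis. All of this stands, and it narrows the route to individual consent and encouragement. It does not close that route, because none of these steps keeps the arm from the recruiter or the patient before consent and baseline.

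A reader might infer from Plans to promote participant retention and complete follow-up {18b} that champions shaped who joined in the pilot. The text does not support this. It says "These nurse champions influenced the rates of recruitment within each haemodialysis centre", which concerns how many joined, not which patients.

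The magnitude is also open to challenge. Both inputs are assumed, and the formula supposes no baseline covariate. Section {20a} names stratification factors and clustering, but the SAP, which is not shown, may add baseline EQ-5D-5L. That would remove much of the measured part, though not unmeasured selection.

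Lastly, later disclosure is not free. Linked parent and satellite sites share an arm because patients move between them (Trial design {8}), so disclosure at one could reveal the arm at another that is still recruiting. Recruitment also began in April 2021, before publication. Both points stand as costs of the fix.

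**Conclusion.** The point holds as a risk to the primary comparison that the design could reduce. It rests on one inference, that site initiation precedes recruitment, which the arm-specific baseline survey makes the natural reading.

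The 0.008 to 0.020, or 11% to 29% of the 0.07 target, illustrates what modest selection could do to an unadjusted change score. It is not an estimate. A reader might go further and conclude that the arms are already unbalanced or that the result will be biased by this amount. The article contains no evidence of either, and it fixes neither the direction nor the size of any selection.

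The change is worth making where it is still possible, because it needs no more patients and leaves the sample size as it is.

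**What to change.** **Clusters not yet initiated.** Use one baseline survey in both arms: consent, EQ-5D-5L, SONG-HD Fatigue and the fidelity questions. Withhold the allocation from unit staff and participants until the 2-week recruitment period and the baseline survey have closed at all linked sites in the cluster. In intervention units, give the first IPOS-Renal at a following dialysis session within its 2-week window, and state the date from which that window runs. This is workable because the common measures are the same in both arms and patients attend about three times a week.

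**All clusters, including those already opened.** Report consenters against all eligible registry patients by arm. Representativeness reporting is already planned, so only the split by arm is new, at almost no cost.

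**Analysis.** If the SAP does not already include baseline EQ-5D-5L as a covariate, adding it would deal with much of the measured imbalance. It does not replace later disclosure.

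**Cost.** The baseline survey is split, and arm-specific training needs a later contact. Windows must be synchronised within linked clusters. Early and late sites will differ in baseline procedure, which should be recorded and reported. Recruitment was planned to run until September 2023, so the benefit is limited to clusters initiated after the change.
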